**Enrollment:**							
Eligibility screen	X						
Informed consent	X						
History and ECG	X						
Allocation		X					
**Interventions:**							
Medical treatment*****			X				
Invasive treatment strategy				X			
**Assessments:**							
Echocardiography and frailty score	X						
QoL and angina questionnaire	X						X
Adverse events				X	X	X	X
If symptoms, additional assessments****					X	X	X
**Outcome:**							
MACCE*****						X	X^§^
Myocardial infarction							X
All-cause mortality							X
**Safety measure: bleeding**				X	X	X	X

*Medical treatment will be given to all study participants regardless of treatment allocation, provided that there are no contraindications.

**If symptoms of ischemia: ECG, CK-MB, and cardiac troponins. If symptoms of bleeding: hemoglobin and platelet count.

*********Combined endpoint: MACCE: major adverse cardiac or cerebral event.

^§^Primary endpoint of the study.

QoL: Quality of life, ECG: Electrocardiogram.

### Reporting of adverse events

According to Swedish legislation, the investigator is responsible for reporting of safety information to local authorities. An adverse event (AE) is any unfavorable sign or symptom associated with the study agents or the coronary intervention. A serious adverse event (SAE) is defined as any AE occurring that results in: death, a life-threatening event, the prolongation of existing hospitalization or new unplanned hospitalization, persistent or significant disability, or intracranial hemorrhage.

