### Study objectives and hypothesis

This randomized controlled trial (RCT) aims to address a fundamental question: which treatment strategy in elderly patients with myocardial infarction results in a better outcome with acceptable risk? Specifically, which treatment strategy improves survival and results in less morbidity and better quality of life? Equally important are the adverse events associated with each treatment strategy.

We hypothesize that revascularization in elderly patients with ACS will lead to gain in terms of outcome and quality of life compared to medical therapy alone. Secondly, we hypothesize that adverse events will occur, but will be within an acceptable range.

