## Methods/Design

### Design of trial

The octogenarians study is an academically sponsored and principal investigator-initiated study. The study design adheres to the ‘CONsolidated Standards of Reporting Trials’ (CONSORT) statement [6].

The study is a phase 4 RCT with two parallel treatment arms: invasive therapy and medical therapy. Invasive therapy will include a coronary angiography and, if feasible, revascularization with percutaneous coronary intervention (PCI) or coronary artery bypass grafting (CABG). Blinding of study participants is not possible due to the invasive treatment arm, which makes the trial an open-label trial.

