### Crossover

Efforts should be made to keep the initial treatment allocation, but a certain crossover rate can be expected. Patients randomized to the invasive treatment group will receive medical treatment in case of coronary anatomy unsuitable for intervention. Patients in the medical treatment group will undergo coronary angiography with possible revascularization in case of ischemia leading to refractory chest pain, hemodynamic instability (including cardiogenic chock), heart failure, or life-threatening cardiac arrhythmias.

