### Intervention procedures

*Invasive treatment (intervention arm of the RCT)*: coronary angiography will be performed with the use of 5 to 8 F catheters via the femoral or radial approach at the operator’s discretion. Revascularization with PCI or CABG will be performed if feasible and if acceptable to the patient. For all patients, standard medication (as mentioned below) will be administered if the patient has no contraindications. If PCI is performed, the patients will be treated with heparin or bivalirudin according to local guidelines and at the operator's discretion. *Medical treatment (control arm of the RCT)*: patients randomized to medical treatment will receive optimized medical treatment and will not undergo a coronary angiography.

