### Trial medication

The following medication is recommended but not mandatory in both treatment arms.

Aspirin will be administered to all patients on a daily basis in a maintenance dose of between 75 and 160 mg. If the patient is previously untreated with aspirin, a loading dose of between 160 and 320 mg will be given.

Other antiplatelet medications include clopidogrel (with a loading dose of between 300 and 600 mg) or ticagrelor (loading dose of 180 mg) will be administered as soon as possible, and always before the coronary angiography, in patients randomized to invasive treatment.

Treatment with a statin (such as atorvastatin) will be started as soon as possible. Beta-blockers are often included as an anti-ischemic treatment in the absence of contraindications. Long-term treatment is recommended in the case of reduced left ventricular function. Nitroglycerin (intravenous, oral, sublingual or buccal) is recommended for symptom relief if necessary. ACE inhibitors are indicated long-term in all patients with heart failure (left ventricular ejection fraction ≤40%) and in patients with diabetes mellitus or hypertension.

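### An adverse event, and hence a serious one, counts only if associated with a study drug or the coronary intervention, so general AE/SAE rates are open to differential ascertainment between the open-label arms

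*Protocol article*

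**What the plan says.** The protocol article, under Reporting of adverse events, gives two linked definitions. The first is "An adverse event (AE) is any unfavorable sign or symptom associated with the study agents or the coronary intervention". The second builds on it: "A serious adverse event (SAE) is defined as any AE occurring that results in: death, a life-threatening event", followed by further seriousness criteria (prolonged or new unplanned hospitalization, lasting disability, intracranial hemorrhage).

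Other sections bear on how these definitions work:

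- **Design of trial:** "Blinding of study participants is not possible due to the invasive treatment arm, which makes the trial an open-label trial".
- **Intervention procedures:** "patients randomized to medical treatment will receive optimized medical treatment and will not undergo a coronary angiography". The Crossover section adds the exception: "Patients in the medical treatment group will undergo coronary angiography with possible revascularization in case of ischemia leading to refractory chest pain", and also for hemodynamic instability, heart failure or life-threatening arrhythmia.
- **Trial medication:** "The following medication is recommended but not mandatory in both treatment arms".
- **Study objectives and hypothesis:** "Equally important are the adverse events associated with each treatment strategy". The abstract also lists adverse events, with bleeding as the example, among the secondary outcomes.
- **Table 1:** adverse events are assessed in hospital, at discharge, at day 30 and at 1 year. Bleeding has its own row as a safety measure.

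**The concern.** The objectives ask about the harms of each *strategy*. The definition collects harms of the *drugs or the intervention*. Harm that follows from not revascularizing fits neither cause, so a literal reader would not record it. The SAE is nested in the AE, so a serious event judged unassociated does not become an SAE either.

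One of the two qualifying causes is largely confined to the invasive arm. The judgement of association is made in an open-label trial, and the article describes no blinded assessor. If the arms differ in how readily events are called associated, recorded AE and SAE rates will differ even when the true rates are equal. The trial would then answer its question about acceptable risk partly from a recording rule.

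**Working it through.** The definition carries no figure of its own. The check is therefore a comparison of sections, followed by an illustration on assumed inputs.

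**1. Which events escape the attribution condition?**

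| Event | Where defined | Needs association? |
|---|---|---|
| Major and minor bleeding | Outcome and safety measurements; Secondary outcome (30 days) | No |
| Death | Definitions (all-cause); Secondary outcome (1 year) | No |
| Myocardial infarction, stroke, unplanned revascularization | Definitions | No |
| Unscheduled hospitalization for chest pain, or for first-onset arrhythmia or heart failure | Definitions | No |
| Heart failure or arrhythmia during the index stay | Only the AE/SAE route | Yes |
| Prolonged index stay | Only the AE/SAE route | Yes |
| Hospitalization for previously known heart failure or arrhythmia | Only the AE/SAE route | Yes |
| Non-cardiac hospitalization (other than for an event above) | Only the AE/SAE route | Yes |
| Lasting disability (other than through an event above) | Only the AE/SAE route | Yes |

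The last five rows are the gap. The Crossover section itself foresees heart failure and serious arrhythmia in the medical arm, so these events are not remote.

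**2. Which way could the bias run?** Neither direction is fixed. Procedural complications can qualify mainly in the invasive arm, which would raise its count. But the abstract describes invasive treatment as angiography plus intervention if feasible, so it is unclear whether a complication of angiography alone is associated with the intervention. Drug-related events qualify in both arms, because medication is recommended in both.

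**3. Illustration of size.** The only input from the article is n = 100 per arm (Sample size). To check the formula, I apply the pooled-variance two-proportion calculation, two-sided 0.05 and 80% power, to the article's 40% versus 20%:

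n = [1.96·√(2·0.30·0.70) + 0.8416·√(0.24 + 0.16)]² / 0.20² = (1.270 + 0.532)² / 0.04 ≈ 81.2, so 82 per group, as the article states.

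Now *assume* a true event rate r equal in both arms, with fractions a₁ (invasive) and a₂ (medical) judged associated. Recorded rates are p₁ = r·a₁ and p₂ = r·a₂, with mean p̄. The chance of a nominally significant difference is approximately

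Φ{ [|p₁ − p₂| − 1.96·√(2p̄(1 − p̄)/100)] / √([p₁(1 − p₁) + p₂(1 − p₂)]/100) }.

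For r = 20%, 80% versus 60%: p₁ = 0.16, p₂ = 0.12, p̄ = 0.14, giving Φ[(0.04 − 1.96·0.0491)/0.0490] = Φ(−1.15) = 0.126.

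| True rate, both arms | Judged associated (invasive vs medical) | Recorded rates | Chance of spurious significance |
|---|---|---|---|
| 20% | 80% vs 60% | 16% vs 12% | 0.13 |
| 30% | 80% vs 60% | 24% vs 18% | 0.18 |
| 40% | 80% vs 60% | 32% vs 24% | 0.24 |
| 20% | 80% vs 40% | 16% vs 8% | 0.41 |
| 30% | 80% vs 40% | 24% vs 12% | 0.60 |
| 40% | 80% vs 40% | 32% vs 16% | 0.76 |

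With 60% versus 80%, the probabilities in the first three rows are the same and the apparent disadvantage moves to the medical arm. With no difference in attribution, the chance is the nominal 5%.

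**The case against.** The strongest reply is that the safety comparison does not rest on this definition. Bleeding, the one item labelled a safety measure in Table 1, is defined by criteria. Death is all-cause, and the main clinical events are defined without reference to cause by treatment. The section concerns reporting to authorities, and the Secondary outcome section lists no AE or SAE rate. The second hypothesis says that adverse events will stay within an acceptable range, which is not a between-arm test. The article neither defines association nor says who judges it, so unblinded causality assessment is inferred from the open-label design.

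Much of this stands, and it rules out two stronger readings that a reader might infer:

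- *That safety as a whole cannot be compared between arms.* The documents do not support this, because the events in the first four rows of the first table can be compared. Hemoglobin after baseline is drawn only when bleeding is suspected, which can affect detection, but that is a separate matter from attribution.
- *That the comparison is tilted against the invasive arm by construction.* Study drugs are given in both arms, medical-arm crossovers also undergo procedures, and the status of angiography alone is unclear. The direction is unknown.

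The reply does not remove the residual gap. The objectives and the abstract make adverse events a study question, Table 1 schedules their assessment separately from bleeding, and the last five rows of the first table have no other route into the data. If association was meant only in time, the text should say so. As written, sites may apply it differently.

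**Conclusion.** The concern holds for general AE and SAE rates only. The definition makes recording depend on a judgement of association, in an open-label trial where one of the two qualifying causes sits mainly in one arm. This does not match the objective of describing the harms of each strategy. The primary outcome, the sample size and the outcomes defined without attribution are unaffected.

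The size cannot be derived from the documents. The 13–24% range rests on assumed equal true rates of 20–40%, an assumed 80% versus 60% attribution, and a between-arm test that the article does not itself specify. It would be higher with stronger asymmetry and absent with none.

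**What to change.** Reword the Reporting of adverse events section and the case report form as follows:

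1. Define an AE as any untoward medical occurrence after randomization, in either arm, regardless of presumed cause.
2. Apply the seriousness criteria already listed to that base.
3. Record relatedness to drug, procedure or disease as a separate field.
4. Compare all-cause SAEs by arm.

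The cost is a wording change and somewhat more entries to record. Trial status says recruitment has run since October 2009, so the sponsor should also state how events in patients already enrolled will be handled, identically in both arms. No change to the sample size or the primary outcome is needed.

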### Outcome

#### Primary outcome

The primary outcome measure is the combined endpoint of a major adverse cardiac or cerebrovascular event (MACCE) within 1 year. Assessments will be conducted during hospitalization, discharge, after 30 days, and after 1 year, as shown in Table 1.

### Secondary outcome

Secondary outcome measures include: any MACCE within 1 month, death at 1 year, any myocardial infarction at 1 year, death or myocardial infarction at 1 year, major bleeding at 30 days, and minor bleeding at 30 days.

### Sample size

According to previous trials, such as the TACTICS-TIMI 18 elderly substudy [3], we expect a MACCE rate of 40% within one year of allocation with the conservative strategy, and that this could be reduced to 20% with an invasive strategy. With 80% power and an α level of <0.05, this trial will require 82 individuals in each group. Due to possible dropout, 200 patients will be included in the trial; 100 in each treatment arm. No interim analysis is planned.

### Data and statistical analysis

Data will be entered into each patient’s case report form (CRF). The principal investigator is the data custodian. Data will be screened and, if necessary, cleaned (the process of detecting and correcting corrupt or inaccurate records from a record set, table, or database) in order to ensure validity and integrity. The statistical analysis will be managed according to the intention-to-treat principle.

## Discussion

This study seeks to determine the efficacy and safety of invasive and medical treatment strategies in elderly patients with ACS. In doing so, the study will advance our understanding of therapy choice in elderly patients with ACS. The different treatment strategies have the potential to reduce angina pectoris and complications, and improve quality of life and survival.

## Trial status

Recruitment to the study commenced in October 2009 and is still continuing to recruit patients. The recruitment of all patients will hopefully be finished in year 2015.

## Abbreviations

ACS: Acute coronary syndrome
MI: Myocardial infarction
PCI: Percutaneous coronary intervention
TnT: Troponin T
TnI: Troponin I
QoL: Quality of life
ECG: electrocardiogram.
